### Randomization

Allocation to one of the study conditions is performed using a ratio of 1:1, with blocked randomization, stratified for academic hospital (Radboudumc and VUmc), gender and diagnosis (colon and rectal cancer). Patients are randomly allocated to the CORRECT intervention or CAU with a computer randomization program developed specifically for this study. Two secretaries who are working at one central location in the Radboudumc and who are not involved in the study have access to this program and carry out randomization, thus ensuring the researcher cannot influence allocation sequence. The outcome of randomization is notified by the researcher to the patient via phone and mail.

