### Sample size

Power calculation for ANCOVA analysis was conducted with G*Power 3.1.3. In order to detect a medium effect size of 0.4 (based on reviews and meta-analyses of psychosocial and cognitive behavioral interventions in cancer survivors) [25, 38–40] with an alpha of 0.05 and a power of .80, a sample size of 190 participants is calculated. To correct for the baseline assessment as covariate the sample size is multiplied with the factor (1- *r*^2^). The *r* gives the correlation between pre-intervention and post-intervention distress. Based on a meta-analysis of pre-intervention distress as a moderator in psychosocial interventions for distress in cancer patients, this is an average of 0.6 [41], resulting in a sample size of 128 patients. Taking into account a dropout rate of approximately 20% a sample of 160 patients (80 patients per condition) will be included at baseline.

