### Statistical analyses

Statistical analyses are being performed using SPSS. Key variables should be evenly distributed between conditions by randomization. To control for that, baseline characteristics are compared between participants in the intervention and CAU conditions with Chi-square (categorical variables) and ANOVA (continuous variables). Variables that are not evenly distributed are used as covariates in the analyses, along with time since end of treatment to control for the possible relationship between time since end of treatment and the level of distress. Analyses are on an intention-to-treat basis. A per-protocol analysis is amongst participants who successfully completed the intervention. ANCOVA-analysis of the change scores in the outcome variables is conducted to calculate differences between the two conditions. Exploratory sub-group analyses are conducted based on ‘time since end of treatment’, ‘age’, and ‘gender’. Caseness of the GSI is used to determine clinical significant improvement. Caseness is indicated if a T-score on the GSI scale > 62, or a T-score > 62 on two of the three clinical subscales. To analyze the difference between the proportions of patients meeting the criteria for clinically significant improvement at T1, chi-square tests are used.

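### The chi-square test of clinically significant improvement at T1 is valid but leaves out baseline GSI; an adjusted logistic model would gain some power on this supportive comparison

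*Protocol article*

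**What the plan says.** All of this is in the Protocol article.

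- **Test for the binary endpoint (Statistical analyses).** "To analyze the difference between the proportions of patients meeting the criteria for clinically significant improvement at T1, chi-square tests are used". No other method is named for this comparison.
- **Endpoint (Statistical analyses).** Improvement is tied to GSI caseness: "Caseness is indicated if a T-score on the GSI scale > 62, or a T-score > 62 on two of the three clinical subscales". The section does not say whether a patient must be a case at T0 to count as improved.
- **Covariates (Statistical analyses).** "Variables that are not evenly distributed are used as covariates in the analyses, along with time since end of treatment". The sentence does not say whether it covers only the ANCOVA or the binary comparison too.
- **Analysis set (Statistical analyses).** "Analyses are on an intention-to-treat basis".
- **Baseline as covariate (Sample size).** "To correct for the baseline assessment as covariate the sample size is multiplied with the factor" (1 - r²), with r = 0.6. This is done for the continuous outcome only.
- **Randomisation.** Allocation is "stratified for academic hospital (Radboudumc and VUmc), gender and diagnosis (colon and rectal cancer").
- **Eligibility.** Entry depends on a Distress Thermometer score of at least 5, not on GSI caseness, so baseline GSI can fall on either side of the caseness cut-off.

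**The concern.** A chi-square test of two proportions has no place for covariates. The plan treats baseline distress as strongly prognostic when it sizes the trial, then fixes a test for the clinical-significance result that sets the baseline score aside. Dichotomising the GSI already costs power, and the unadjusted test gives up more that the trial's own data could recover.

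A chance difference between arms in baseline distress would also go uncorrected here. With 64 per arm, the standard error of the baseline difference is √(2/64) = 0.18 SD. At r = 0.6, a one-standard-error imbalance moves the expected follow-up difference by 0.6 × 0.18 = 0.11 SD, about a quarter of the target effect of 0.4. The covariate rule in the same section is there to deal with imbalance, and a chi-square test cannot apply it.

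**Working it through.** **Inputs from the protocol.** "In order to detect a medium effect size of 0.4"; alpha 0.05 (sidedness not stated, two-sided used here); r = 0.6; dropout about 20%; 160 randomised, hence 128 analysed, 64 per arm.

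**Assumed.** The protocol gives no caseness rate. The non-case rate under usual care at T1 is therefore varied from 20% to 85%. Scores are taken as bivariate normal.

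**1. The plan's own figures.** The two-group size for d = 0.4, two-sided 0.05 and 80% power is 2 × (1.96 + 0.84)² / 0.4² ≈ 98.1, so 99 per arm and 198 in total. A G*Power-type ANCOVA F test gives 199. Then 199 × (1 - 0.6²) = 199 × 0.64 = 127.4, or 128, and 128 / 0.8 = 160. The final figures reproduce. The intermediate 190 does not (190 × 0.64 = 121.6); that is a separate matter and does not affect this point. No power is stated for the binary comparison.

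**2. Chi-square power by formula, one case.** The treated rate follows from p₁ = Φ(Φ⁻¹(p₀) + 0.4). For p₀ = 0.50, p₁ = Φ(0.4) = 0.655 and the pooled rate is 0.578.
- SE under no difference: √(2 × 0.578 × 0.422 / 64) = 0.0873.
- SE under the alternative: √((0.250 + 0.226) / 64) = 0.0862.
- Power: Φ((0.155 - 1.96 × 0.0873) / 0.0862) = Φ(-0.18) ≈ 43%.

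**3. Simulation, T1 caseness analysed in all patients, 64 per arm.** Pearson chi-square against the likelihood-ratio test for arm in a logistic model with continuous baseline score. Gains come from unrounded values.

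| Non-case rate, usual care | Treated | Chi-square | Adjusted | Gain (points) |
|---|---|---|---|---|
| 20% | 33% | 38.6% | 47.0% | 8.4 |
| 30% | 45% | 43.6% | 52.4% | 8.8 |
| 40%* | 56% | 43.2% | 55.2% | 12.0 |
| 50% | 66% | 43.3% | 53.4% | 10.2 |
| 70% | 82% | 36.5% | 45.6% | 9.0 |
| 80% | 89% | 30.1% | 37.7% | 7.6 |
| 85% | 92% | 25.9% | 32.2% | 6.4 |

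*4,000 simulated trials; the other rows use 20,000. With 80 per arm (no dropout) the gain is 7.3 to 12.5 points.

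**4. Improvement read as case at T0, non-case at T1.** Baseline case rate varied from 30% to 85%.
- All randomised patients counted, baseline non-cases as not improved: gain 2.2 to 6.2 points (64 per arm), 1.4 to 5.9 (80 per arm).
- Baseline cases only: 2.7 to 4.6 points (out of 64 per arm), 0.7 to 4.7 (out of 80 per arm).

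**5. Sensitivity to r.** Reading of step 3, 50% usual-care rate, 64 per arm: 4.6 points at r = 0.4, about 10 at 0.6, about 23 at 0.8.

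**6. Where the gain comes from.** Adding only a covariate unrelated to outcome gains 0 to 2 points. Nearly all the gain is from baseline GSI.

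**7. Type I error under no effect.** Chi-square about 4 to 6%. Logistic model with baseline GSI only: about 5 to 6%. With three stratification factors and time since treatment added (assumed non-prognostic): about 5 to 7%. Events can be few: at 20% usual-care caseness there are about 64 × 0.20 + 64 × 0.107 ≈ 20 cases for six non-intercept terms.

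**The case against.** The case for leaving the plan alone has real weight.

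- **The chi-square is valid.** Its type I error is sound. This stands: the point is about efficiency, not error.
- **The endpoint is supportive.** It is not in the primary, secondary or other outcome lists, and the sample size covers only the ANCOVA. Power is low with either test. This also stands and keeps the severity minor.
- **The plan may not contradict itself.** A reader might infer that the covariate sentence and the chi-square sentence cannot both be followed. The text does not establish that. The covariate sentence can be read with the ANCOVA, the only covariate-taking model the section names, and an adjusted continuous analysis beside raw responder proportions is a coherent plan.
- **The size depends on a definition the protocol leaves open.** A reader might infer a flat loss of 7 to 12 points. That needs T1 caseness in everyone and r = 0.6. The intention-to-treat sentence and the absence of a baseline-caseness condition fit that reading, but the word improvement also allows a change from case to non-case. T0 status is then already partly in the outcome and the gain is much smaller.
- **The named covariates are not the source of the gain.** Baseline GSI is not named as a covariate in the Statistical analyses section, and the protocol gives no prognostic strength for those that are. Applying the plan's covariate rule alone need not recover the power.
- **A larger model has a cost.** With few events the full model is slightly liberal, and part of its apparent gain reflects that.

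These objections limit the size and the severity. They do not remove the gain from baseline GSI, which was positive in every setting examined.

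**Conclusion.** The point holds as a cheap improvement of minor severity. The unadjusted test leaves out the T0 GSI score, which the plan itself treats as prognostic. At d = 0.4, r = 0.6 and 64 analysed per arm, adjusting for it is worth about 6 to 12 points of power if T1 caseness is analysed in all patients. If improvement requires being a case at T0, it is worth about 1 to 6 points (the lower end comes from the runs with 80 per arm). All these figures rest on assumed caseness rates and normal scores.

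The documents do not support calling the chi-square wrong, describing the covariate sentence as a definite contradiction, or suggesting that the trial's primary power is at risk. If the continuous and binary results diverge, adjustment could be only part of the reason, since dichotomisation alone can also produce it.

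**What to change.** Replace the chi-square sentence with a logistic regression of T1 status on arm, continuous baseline GSI and time since end of treatment. Add the stratification factors (academic hospital, gender, colon or rectal cancer) only if the number of events supports them. Report the standardised risk difference with its 95% CI, and keep the raw proportions as description. State in the same place whether the covariate rule covers this comparison and whether improvement requires caseness at T0.

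The cost is a sentence or two of analysis text and a standard SPSS procedure on data already collected, with no extra patients. There are two drawbacks. The odds ratio is conditional on the covariates, which the standardised risk difference resolves. With few events the likelihood-ratio test of the full model is slightly liberal (about 5 to 7% in simulation), so the covariate set should stay small or a small-sample correction be used.

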### Monitoring

Data monitoring and quality assurance is conducted on a annual basis by a data monitor who is independent from the researchers and the funding body and who is employed within the Department of Medical Psychology, Radboud University Medical Centre. Annually the data monitor completes a quality monitoring document based on an interview with the researchers regarding: contact to ethical committee, study participation and design, paper and digital archives, data-analyses and controlling Informed Consent forms, Source Data Verification and Serious Adverse Events (SAE’s). SAE’s have to be reported to the ethical committee CMO Arnhem-Nijmegen by a standard procedure.

## Discussion

Approximately one third of the CRCS experience high levels of psychological distress. Due to the rising numbers of CRCS, widely accessible and evidence-based supportive care is needed to deal with this growing need. This protocol paper describes the CORRECT multicenter trial which evaluates a blended CBT intervention (CORRECT) for reducing high psychological distress in CRCS. The primary objective is to evaluate the efficacy and cost-effectiveness of the CORRECT intervention in decreasing psychological distress in CRCS. To our knowledge, this is the first blended psychological intervention with self-management elements which is specifically aimed at reducing psychological distress amongst CRCS.

CRCS are an under-served population with respect to psychosocial supportive care research. Few studies investigate psychological interventions specifically designed for CRCS. The CORRECT study addresses this gap in current research. Most studies on distress and psychosocial interventions over-represent women with breast cancer [25]. Interventions that might be proven to be effective for women with breast cancer may not be as effective for males or for survivors of other tumor types. Within CRCS samples gender may be an important mediator of the efficacy of psychological interventions. In the current study we both include male and female CRCS, which makes it possible to explore possible differences in our mixed group.

Reviews indicate that psychological interventions are most effective for patients who are pre-selected for high distress [25, 41]. In order to identify highly distressed patients, every CRCS at participating sites who scores above cut-off on the nationally mandated DT (≥ 5) will be offered inclusion in the CORRECT study. The CORRECT intervention is therefore highly-specialized and tailored care to help CRCS deal with their unique problems of survivorship. This may be a strength, however it may also be a barrier. A study by Van Scheppingen and colleagues [85] found implementing screening to be inefficient for recruiting distressed cancer survivors to a RCT. They found need for psychological services to be much lower than they anticipated before the start of the trial. In another study it was concluded that, “depending on the clinical context, screening might be more efficient if unmet needs for services are assessed rather than psychological distress” [86]. We try to obviate this issue by using a telephone protocol in which the researcher will go through the completed DT with the patient and verbally confirm there is a need for a psychological intervention. Further, we expect our retrospective recruitment method to overcome this issue by first asking if a patient is willing to participate in the trial and then screening the patient for high distress level. An additional strength of this trial is that it is conducted using a rigorous methodology and in accordance with CONSORT guidelines. Patient recruitment is conducted in different hospitals (both regional and academic hospital settings) in two regions of the Netherlands, which may enhance its generalizability. Furthermore, it is delivered by experienced therapists who are working in clinical practice and not therapists specially recruited and trained for therapy delivery in academic centers. This will facilitate implementation should the therapy be proven effective.

The CORRECT intervention is developed in close collaboration with patients from the participating hospitals and patient representatives from patient organizations. CRCS have been involved in different phases of the research and intervention development. A pilot study has demonstrated that the screening procedure is feasible and acceptable to CRCS. Patient participation in the CORRECT study helps to ensure that the intervention is provided in a manner consistent with patient needs and preferences. Further, we aimed to use the person-based approach to ground our intervention design as intended: “in a rigorous, in-depth understanding of the psychosocial context of the people who will use the intervention” [87]. Taking the needs and experiential knowledge of patients into account is considered to result in the improvement of individual health care [88]. Patient participation in the intervention development will help ensure the intervention is provided in a manner consistent with patient needs and preferences. If proven effective, this will increase the likelihood of high uptake when implemented in routine care.

A secondary objective of the CORRECT study is to investigate the use of online activities and how website usage is associated with distress reduction, in accordance with usage evaluation in a previous study of online self-management intervention for breast cancer survivors [84]. Usage evaluations are relatively new and growing area of interest in online intervention research. Analysis of usage data provides information on which patient subgroups experience the greatest benefits. This facilitates knowledge about personalizing psychosocial interventions for CRCS and further a growing body of research on the relationship between e-health interventions and psychological and behavioral change.

In conclusion, the CORRECT intervention is a promising method of reducing psychological distress, improving QoL and enhancing personalized supportive care for CRCS. Should this trial prove its efficacy, the ultimate goal will be to implement and disseminate the CORRECT intervention nationally and internationally.

## Abbreviations

CAU: Care as usual
CBT: Cognitive behavioral therapy
CMO: Medical ethical committee
CRC: Colorectal cancer
CRCS: Colorectal cancer survivor(s)
F2F: Face-to-face
FCR: Fear of cancer recurrence
QoL: Quality of life
Radboudumc: Radboud University Medical Center
RCT: Randomized controlled trial
VUmc: VU University Medical Center
